### **Brachial Blood Pressure**

The brachial systolic blood pressure (SBP) and diastolic blood pressure (DBP) will be measured with the participants in the supine position using an automated oscillometric cuff (Bosotron 2®, Bosch & Sohn, Germany) in all measurement rounds. Two measurements will be taken and if these values deviated by >5 mmHg, a third measurement is performed. The average of the two closest values will be used.

### **Arterial Stiffness**

#### **Aortic and Limb Arterial Stiffness**

Arterial stiffness as measured by pulse wave velocity (PWV) obtained by applanation tonometry will be measured in all measurement rounds. A single operator locates the carotid, femoral, radial and distal posterior tibial arteries on the right side of the body and mark the point for capturing the corresponding pressure curves with two specific pressure sensitive transducers. The distance between the carotid and femoral, radial and distal posterior tibial arteries is measured directly and entered into the Complior Analyse software (ALAM Medical, Paris, France). Right brachial blood pressure is measured and entered into the Complior Analyse software, and then signal acquisition is launched. The operator positions the carotid sensor with the help of its specific holder and manually held the femoral sensor on the femoral artery and the distal sensor in the distal posterior tibial artery. When the operator observes 10 carotid pulse waveforms of sufficient quality, simultaneous carotid and femoral, radial and distal posterior tibial pressure curves are recorded for 10 pulse waveforms. The time delay (aortic transit time) between the two pulse waveforms is then calculated automatically. Values obtained from the carotid to femoral artery, carotid to radial artery and carotid to distal posterior tibial artery will be taken as indices of central/aortic, upper and lower limb arterial stiffness, respectively.

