## **Purpose**

The aim of this study was to compare the time-course of post-exercise parasympathetic reactivation of the heart and changes in local and regional indices of arterial stiffness to different fitness classes (Bike, Pump Power and Global Training), as prescribed for health [34] and commercially available.

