### **Statistical Analysis and Data Monitorization**

Based upon a medium effect size of 0.154 derived from published changes in aortic PWV within-between modes of exercise [18], an a priori power analysis suggested that 22 participants are required to detect significant differences within-between groups, conditions and time points ( $1-\beta = 80\%$ ,  $\alpha = 0.05$ ). All data will be collated and/or analyzed using Microsoft Excel (v15.29.1, Microsoft Corporation, Redmond, Washington, United States) and Statistical Package for the Social Sciences version 24 (IBM, Armonk, New York, United States) software with results presented as mean  $\pm$  SD. Due to technical issues, missing data (~4–5%) may be evident during the study and subsequently should be replaced by averaging values before and after the missing value for the relevant variable prior to analysis.

Comparisons between interventions (Bike, Pump Power, Global Training and Control) over time (Rest vs. post-intervention time points) for indices of autonomic and vascular function will be examined via two-way

(intervention × time), repeated measures analysis of variance (ANOVA) and adjusted for sex and activity energy expenditure. Session differences for indices of autonomic and vascular function and energy expenditure will be analyzed using a one-way repeated measures ANOVA. Post-hoc comparisons will be conducted via Bonferroni's tests. Statistical significance will be set at  $p < 0.05$ .

The database will be stored in the GCP private server throughout the study period. The GCP lab will be responsible for management, storage and is the single user of the complete database.

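### The lower-limb stiffness index (carotid-to-tibial PWV) includes the segment the protocol itself calls aortic, so it cannot separate a leg response from an aortic one

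*Protocol*

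**What the plan says.** The Protocol, Aortic and Limb Arterial Stiffness, defines three PWV indices, all timed from the carotid. Carotid-femoral stands for the aorta and carotid-radial for the arm; the third is stated thus: "carotid to distal posterior tibial artery will be taken as indices of central/aortic, upper and lower limb arterial stiffness, respectively".

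The inputs are described in the same section. On distance: "The distance between the carotid and femoral, radial and distal posterior tibial arteries is measured directly and entered into the Complior Analyse software". On acquisition: "simultaneous carotid and femoral, radial and distal posterior tibial pressure curves are recorded for 10 pulse waveforms". On timing: "The time delay (aortic transit time) between the two pulse waveforms is then calculated automatically". No femoral-tibial PWV is planned, and no subtraction of the aortic segment is described.

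The Purpose section makes the comparison of "local and regional indices of arterial stiffness" between classes part of the aim. The Design section likewise announces regional PWV for separate arterial territories. The Statistical Analysis section tests vascular indices with a two-way repeated-measures ANOVA of intervention by time.

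**The concern.** A regional index is useful only if it responds to its own region. Here the lower-limb index and the aortic index share a segment, and nothing in the plan removes it from the former.

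The overlap matters because the protocol expects the aorta to move. Its background section (Descriptive Elements of the Project) says that a single exercise bout reduces aortic PWV, and that the few direct comparisons found different responses by exercise mode. If aortic PWV changes differently after Bike, Pump Power and Global Training, the carotid-tibial index will also differ between them, even if leg arteries respond alike. The ANOVA would then show an intervention-by-time effect for the lower limb that is partly or wholly aortic. Conversely, a genuine leg-only effect would appear smaller than it is.

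**Working it through.** The protocol states no path length, velocity or transit time, so there is no figure to reproduce. The overlap itself follows from the definitions alone. Only its size needs assumptions.

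**Assumed ranges (not from the documents), healthy young adults**
- Carotid-femoral path La = 0.48-0.65 m, velocity Va = 5.5-8 m/s
- Femoral-tibial path Ll = 0.75-0.95 m, velocity Vl = 8-11 m/s

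Three values of each were crossed, giving 81 combinations.

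**Formulas**
- Carotid-tibial PWV = (La + Ll) / (La/Va + Ll/Vl)
- Aortic share of transit time s = (La/Va) / (La/Va + Ll/Vl)
- If leg PWV alone falls 10%, the leg delay is divided by 0.9, and the index reads 1/(1 + (1 - s)/9) - 1.
- If aortic PWV alone falls 10%, the index reads 1/(1 + s/9) - 1.

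**Aortic share**
- Middle values: 0.56/6.5 = 86.2 ms and 0.85/9.5 = 89.5 ms, so s = 86.2/175.6 = 0.49.
- Lowest: 0.48/8 = 60.0 ms and 0.95/8 = 118.8 ms, so s = 0.34.
- Highest: 0.65/5.5 = 118.2 ms and 0.75/11 = 68.2 ms, so s = 0.63.
- Median over the 81 combinations 0.48; middle 80% of them 0.41-0.56.

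**What the planned lower-limb index would read**

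| True change | Middle values | Range |
|---|---|---|
| Leg -10%, aorta unchanged | -5.4% | -3.9% to -6.9% |
| Aorta -10%, leg unchanged | -5.2% | -3.6% to -6.6% |
| Aorta +10%, leg unchanged | +4.7% | +3.1% to +6.1% |
| Leg -10%, aorta +10% | -1.2% | -4.2% to +1.7% |
| Leg -10%, aorta -10% | -10% | -10% |

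The second row is computed from the formula above: 0.4905/9 = 0.0545 gives -5.2%; 0.3357/9 = 0.0373 gives -3.6%; 0.6341/9 = 0.0705 gives -6.6%. In the same model, the index obtained by subtraction reads -10% when the leg changes by -10%, whatever the aorta does.

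**Noise of the subtracted index.** Assume a 2 ms error on each delay, and take 0.50 m at 6.5 m/s (76.9 ms) and 0.85 m at 9 m/s (94.4 ms), total 171.4 ms.
- Planned carotid-tibial index: 2/171.4 = 1.2%.
- Subtracted, sequential recordings with independent errors: sqrt(2) × 2/94.4 = 3.0%.
- Subtracted, simultaneous recordings: the carotid time enters both delays and drops out. If the three sites are timed equally well, the error of the difference stays at 2 ms, or 2/94.4 = 2.1%.

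A 10% fall in leg PWV adds 94.4/0.9 - 94.4 = 10.5 ms to either index. Signal over error is therefore 10.5/2 = 5.2 for the planned index, 5.2 for the subtracted index with simultaneous curves, and 10.5/2.8 = 3.7 with sequential ones.

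**The case against.** The strongest counter-argument concerns precision. A diluted percentage does not mean lost power: the leg signal in milliseconds is the same in both indices, and subtracting two independently measured delays only adds error. In a study planned for twelve participants (Participants section) or 22 (Statistical Analysis section), that counts. It stands fully if the recordings are sequential. It largely falls away if they are simultaneous, because the carotid timing error then cancels. The protocol leaves this open: it mentions a pair of transducers and a delay between two waveforms, yet also calls the carotid, femoral, radial and tibial curves simultaneous. In either case, greater precision does not show which segment changed, and that is the regional question.

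A second argument is that carotid-femoral PWV is reported alongside, so a careful reader can see when an apparent leg change might be aortic. This limits the harm, but leaves the reader to do informally what one derived variable does directly.

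Some stronger readings are tempting and are not supported:
- That half of the index is aortic. The documents give no figure; the share depends on assumed lengths and speeds.
- That leg and aortic responses will cancel. This needs changes in opposite directions, which the protocol does not predict. Dilution or misattribution is the more likely harm.
- That the aorta is counted twice. The indices are separate outcomes and are never summed.
- That Bike is a leg class set against others. The Intervention sessions section does not classify the classes by limb.

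**Conclusion.** The point holds, within limits. The protocol's lower-limb PWV index includes its own aortic segment, so it mixes the two responses and carries a label it does not earn. This needs no outside figure, and it is not a detail left to an analysis plan, because the protocol fixes the definition.

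The size rests on the assumed ranges above: an aortic share of about 34-63%, centred near 48%, with a leg-only change of -10% reading as about -4% to -7%. At no point in those ranges is the aortic part negligible.

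A reader might infer that the regional stiffness results as a whole are compromised. They are not. Carotid-femoral PWV is untouched, and the sample size calculation is based on aortic PWV. The change is worth making because it corrects the only PWV index offered for the lower limb, using measurements already planned.

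**What to change.** In Aortic and Limb Arterial Stiffness, define the lower-limb index as

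femoral-tibial PWV = (carotid-tibial distance - carotid-femoral distance) / (carotid-tibial delay - carotid-femoral delay).

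Keep carotid-tibial PWV as a supplementary index, labelled aorta plus leg.

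In the same section, reconcile the two-transducer description with the statement that the curves are simultaneous, and say which sites are captured together. If they are sequential, report both indices side by side, since the subtracted one is then noisier (about 3.0% against 1.2% under the assumed 2 ms error) and its two delays come from different beats.

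The cost is one derived variable, a relabelling and a somewhat noisier index. No additional measurement is needed.

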#### **Carotid Blood Pressure**

Carotid Systolic Blood Pressure (cSBP) will also be assessed by applanation tonometry (Complior Analyse) in all measurement rounds, from right carotid traces acquired during the carotid pulse wave velocity (cPWV) assessment. The waveforms will be averaged and the mean values will be extracted from 15 s window of acquisition. The carotid waveforms are calibrated from MAP and bSBP, measured immediately before the acquisition.

#### **Carotid Arterial Stiffness Indices**

The severity of Cardiovascular disease is likely to be reduced if atherosclerosis is detected early and before morphologic changes such as plaque and wall thickening are visible in the arterial walls. Prevention and treatment of lifestyle-related diseases are increasingly important today, and so the role of the ultrasound diagnostic system is not only to observe the morphologic changes but also to perform functional assessment. Hitachi Aloka realized functional assessment of arteries by developing our unique eTRACKING technology.

eTRACKING achieves highly precise measurements of the vessel distension in real time, using radio frequency (RF) signals. Conventionally, vessel diameters are measured visually on B-mode and M-mode images, this can lead to variations in the measurement because it is difficult to know time-dependent changes in the vessel diameter on B-Mode. Furthermore, it is difficult to identify exact timing for the measurement of the maximum and minimum diameter. To overcome these problems in measuring vessel diameter, eTRACKING has been developed and implemented in a diagnostic Ultrasound system.

Common carotid diameter values and diameter-derived pressure data will be used to calculate established indices of local arterial stiffness, such as the Peterson's pressure-strain elastic modulus ( $\epsilon$ ) and the stiffness index ( $\beta$ ), according to published algorithms [51], in all measurement rounds.

$$\epsilon = [(P_s - P_d) / (D_s - D_d)] \times D_d,$$

and

$$\beta = \ln(P_s / P_d) / (D_s - D_d) / D_d,$$

where  $P_s$  and  $P_d$  are systolic and diastolic pressure, respectively, and  $D_s$  and  $D_d$  are the maximum and minimum arterial diameters measured by wall tracking of the intima-media borders of the carotid artery.

The augmentation index (AIx), a surrogate measure of arterial wave reflection from the periphery, expressed as a ratio of the “augmented pressure” (*i.e.*, the pressure difference between the “shoulder” of the carotid artery pressure curve and the peak carotid systolic pressure) to the pulse pressure, will also be calculated from the diameter-derived pressure waveform using the third derivative method to identify the carotid pulse inflection point [52].

### **Carotid Blood Pressure Wave Intensity**

The heart and the arterial system constantly interact with each other through forward travelling waves and reflected waves. Wave Intensity (WI) is calculated as the product of the derivatives of the simultaneously recorded blood-pressure changes and blood-flow-velocity changes. Wave Intensity can be obtained at an arbitrary point in the circulatory system. Blood pressure change waveform is conventionally measured invasively. Hitachi has developed a system to calculate blood pressure change noninvasively and with a high level of accuracy. Based on the similarity of the cyclic blood pressure change and its simultaneous vessel diameter change, a blood pressure waveform is derived non-invasively. This non-invasive pressure waveform can then be analyzed further. WI is a new hemodynamic index which is potentially useful for analyzing interaction of the cardiovascular system, including contraction and dilatation characteristics, influence of reflected waves from peripherals, interaction of elastic and resistance vessels and an index related to time.

The right common carotid artery will be scanned with a Arietta V60 ultrasound machine (Hitachi Aloka Medical Ltd, Mitaka-shi, Tokyo, Japan) using a 7.5-MHz linear array probe incorporating a 5-MHz Doppler transducer in all measurement rounds. In longitudinal view, the probe will be manipulated so that the intima of the artery is imaged clearly from both the anterior and posterior walls, and a single scan line is aligned perpendicularly to the vessel walls at a site 20 mm proximal to the carotid bulb. On-screen cursors will then be placed on the anterior and posterior intima-media borders to enable tracking of both walls. The corresponding displacement waveforms and diameter curve will thus be calculated using high-resolution online wall tracking (“E-track” technology), with a sampling rate of 1 kHz.

Arterial pressure waveforms will be obtained automatically in real time by calibrating peak and bottom values with systolic and diastolic blood pressure measured with sphygmomanometry, as previously validated [53].

Next, a pulse wave Doppler ultrasound beam will be aligned to the vessel walls at the site of acquisition of the diameter waveform, to simultaneously acquire velocity data from a color flow Doppler box covering the entire vessel lumen at an angle of insonation between 60 and 65 degrees, with a sampling rate of at least 50 Hz. Spatially-averaged flow velocity will be calculated from the mean of the color Doppler data [54]. Arterial diameter and velocity will be recorded continuously for 20 s. After completing the acquisition, all data is displayed and any individual beats with noisy or unrepresentative waveforms will be rejected; all other beats (typically about 20) will be selected and signal-averaged to give single waveforms of diameter and velocity [55]. Averaged vectors for pressure and velocity, together with the electrocardiogram, and calculated net WI will be automatically displayed by the software.

## **Benefits**

### **Impact of project on participants and participating organizations**

#### **Impact of PUMPING ARTERIES on the participants**

The health-related components of physical fitness have a strong relationship with overall health, are characterized by an ability to perform activities of daily living with vigor, and are associated with a lower prevalence of chronic disease and health conditions and their risk factors [34]. The information obtained from health-related physical fitness testing in PUMPING ARTERIES will:

- Educate participants about their present health/fitness status relative to health-related standards and age and sex-matched norms.
- Provide data that are helpful in development of individualized exercise prescriptions to address all health/fitness components.
- Motivating participants to establish reasonable and attainable health/fitness goals

In addition, increasing evidence points out at vascular stiffness (and in particular aortic stiffness measured by pulse wave velocity) as a reliable biomarker of vascular aging, able to integrate in a single measure the overall burden of cardiovascular risk factors on the vasculature over time [56]. Increased aortic stiffness has been shown to predict future cardiovascular events and improve risk reclassification in those at intermediate risk. In PUMPING ARTERIES, participants will have the opportunity to learn basic aspects of physiology of large artery stiffness and will be given personalized feedback on the clinical significance of the measured values compared to standards and age and sex-matched norms.

#### **Training of specialists in the areas of research, technology and health services**

Undergraduate health-science education has been undergoing a much-needed transformation to better prepare learners to provide care in complex health systems and to address anticipated workforce needs. Curricular structure and pedagogy have also been evolving with more schools challenging classic structures [67]. What is currently needed of undergraduate health-science education is to create a 21st century multidisciplinary workforce that is able to improve the health of patients and communities. Therefore, Health Science schools should additionally refocus research priorities on areas that will alter public health and patient outcomes, rather than focusing primarily on areas that have little if any utility for the majority of

the population. Thus, PUMPING ARTERIES represents a balance between workforce preparation and research suited to the needs of our communities. PUMPING ARTERIES will allow train and constitute a valuable workforce of specialized technicians, teaching them the right kind of content and competencies, using the best techniques.

### **Fostering harmonization between university and business**

A general and uncontested view is that the research at PUMPING ARTERIES is also motivated by its relevance for education and teaching. Research should contribute to the actuality and the quality of education as well as the anchoring of education in professional practice.

Students may gain experience of applied research and experimental development through which they may enhance their competencies in the world of work. There is some evidence to support the view that students who participated in research projects or were exposed to enquiry-based learning enhanced their competencies regarding problem statement, analytical thinking, and taking a more independent perspective – all qualifications highly rewarded by employers [39]. But for those already in working life the research function of PUMPING ARTERIES is also an important dimension in enhancing key competencies. Universities may employ part-time master students in PUMPING ARTERIES for example. These students carry out real research work applied in a business setting. This enriches their education by providing additional practical and research experience. This is beneficial for PUMPING ARTERIES, GCP or any other employment organization concerned.

### **Privacy and Confidentiality**

In order to assure the confidentiality of the participants, an identification code will be attributed to each participant in the database and all the equipment's and sheets used.

Each participant or its tutor will sign an informed consent authorizing the use of the provided contact details on a follow-up contact to schedule a new measurement round.

### **Storage**

The database will be stored in the GCP private server.

Patient's individual reports will be completed after last assessments, including, but not limited to, quantitative and qualitative information on the following tests: aerobic fitness, body composition, arterial stiffness, resting and activity energy expenditure.

### **Statistical Analysis and Data Monitorization**

Based upon a medium effect size of 0.154 derived from published changes in aortic PWV within-between modes of exercise [18], an a priori power analysis suggested that 22 participants are required to detect significant differences within-between groups, conditions and time points ( $1-\beta = 80\%$ ,  $\alpha = 0.05$ ). All data will be collated and/or analyzed using Microsoft Excel (v15.29.1, Microsoft Corporation, Redmond, Washington, United States) and Statistical Package for the Social Sciences version 24 (IBM, Armonk, New York, United States) software with results presented as mean  $\pm$  SD. Due to technical issues, missing data (~4–5%) may be evident during the study and subsequently should be replaced by averaging values before and after the missing value for the relevant variable prior to analysis.

Comparisons between interventions (Bike, Pump Power, Global Training and Control) over time (Rest vs. post-intervention time points) for indices of autonomic and vascular function will be examined via two-way

(intervention × time), repeated measures analysis of variance (ANOVA) and adjusted for sex and activity energy expenditure. Session differences for indices of autonomic and vascular function and energy expenditure will be analyzed using a one-way repeated measures ANOVA. Post-hoc comparisons will be conducted via Bonferroni's tests. Statistical significance will be set at  $p < 0.05$ .

The database will be stored in the GCP private server throughout the study period. The GCP lab will be responsible for management, storage and is the single user of the complete database.

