## **Methodological Procedures**

### **Participants**

Twelve apparently healthy adults aged between 21 to 34 years will be included in this study. These will be recruited from the professional network of GCP. We do not expect these adults to be enrolled in any other scientific study besides PUMPING ARTERIES. Informed written consent will be signed by volunteers prior to the first evaluation day (Figure 1) in accordance with approval by the Ethical Committee of Faculdade de Motricidade Humana – Universidade de Lisboa. We expect recruited participants to be outwardly active with some experience in both aerobic and resistance exercise (~3–4 times/week, >3 months). No trained athletes will be included in the cohort. All participants will be healthy or perceived to be healthy based on the sport's medical examination or the preparticipation screening process. Exclusion criteria include any form of cardiovascular disease, more than one cardiovascular disease risk factor, resting hypertension (systolic blood pressure >140 mmHg, diastolic blood pressure > 90 mmHg), any prescription medication use, and currently smoking.

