### **Design**

The study is constructed as a randomized, cross-over, repeated-measures intervention. Participants will attend 4, separate, intervention sessions consisting of one group class of Bike, Pump Power, Global Training or no exercise (CON). There will be a minimum of 72 h between sessions [18, 37], and each session will consist of initial rest, experimental intervention, and recovery (Figure 1). Participants will be advised not to engage in any strenuous physical activity at least 48 hours before the study days. Body composition and cardiorespiratory fitness for each participant will be evaluated prior to- and following to- the CON session, respectively.

|                           | WEEK 1 |   |   |   |   |   |   | WEEK 2 |   |   |   |   |   |   | WEEK 3 |   |    |    |    |    |    |
|---------------------------|--------|---|---|---|---|---|---|--------|---|---|---|---|---|---|--------|---|----|----|----|----|----|
|                           | 1      | 2 | 3 | 4 | 5 | 6 | 7 | 1      | 2 | 3 | 4 | 5 | 6 | 7 | 8      | 9 | 10 | 11 | 12 | 13 | 14 |
| ENROLLMENT         |        |   |   |   |   |   |   |        |   |   |   |   |   |   |        |   |    |    |    |    |    |
| Eligibility Screen        |        |   |   |   |   |   |   |        |   |   |   |   |   |   |        |   |    |    |    |    |    |
| Randomization             |        |   |   |   |   |   |   |        |   |   |   |   |   |   |        |   |    |    |    |    |    |
| Informed Consent          |        |   |   |   |   |   |   |        |   |   |   |   |   |   |        |   |    |    |    |    |    |
| INTERVENTIONS*     |        |   |   |   |   |   |   |        |   |   |   |   |   |   |        |   |    |    |    |    |    |
| Bike                      |        |   |   |   |   |   |   |        |   |   |   |   |   |   |        |   |    |    |    |    |    |
| Pump Power                |        |   |   |   |   |   |   |        |   |   |   |   |   |   |        |   |    |    |    |    |    |
| Global Training           |        |   |   |   |   |   |   |        |   |   |   |   |   |   |        |   |    |    |    |    |    |
| Control                   |        |   |   |   |   |   |   |        |   |   |   |   |   |   |        |   |    |    |    |    |    |
| ASSESSMENTS        |        |   |   |   |   |   |   |        |   |   |   |   |   |   |        |   |    |    |    |    |    |

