**FIGURE 1: TIMELINE AND MAIN OUTCOME VARIABLES OF PUMPING ARTERIES**

\* INTERVENTIONS WILL BE RANDOMIZED. THE TIMELINE HEREIN DISPLAYED IS MERELY A GRAPHIC REPRESENTATION OF A PARTICIPANT'S ACTIVITIES FOLLOWING RANDOMIZATION.

In each session, participants will initially undertake 20-min of supine rest on a cushioned examination table with resting energy expenditure measured by indirect calorimetry (K5, Cosmed, Rome, Italy) and heart rate and blood pressure recorded continuously using digital plethysmography technique (Finapres® Nova, Ohmeda, 2 Louisville, Colorado, USA), followed by regional assessments of PWV and pulse wave analysis of the aortic, brachial and femoral arteries on the right side of the body using applanation tonometry (Colson Analyze, ALAM Medical, Paris, France), and carotid arterial stiffness indices and wave intensity analysis using an ultrasound (Arietta V60, Hitachi Aloka Medical Ltd, Mitaka-shi, Tokyo, Japan). In the time following, participants will perform one of three exercise sessions (Bike, Pump Power or Global Training). Exercise sessions will consist of either a 45-minute class of Bike, Pump Power, and Global Training, while energy expenditure will be continuously measured by indirect calorimetry (K5, Cosmed, Rome, Italy) (Figure 2). These sessions are characterized by distinct metabolic demands, representing the typical sessions provided by gyms and health clubs to improve or maintain cardiovascular health. In the control condition, the participants will remain quietly seated for 45-min, maintaining a good posture. Only one participant will be tested per class with approximately 10-20 non-research participants also performing each group fitness class alongside the research participants. Upon completion of each intervention/session, participants will return immediately to the examination table and recover in the supine position for 30-min while hemodynamic and stiffness indices are reevaluated at 10, 20- and 30-min following recovery and compared to those at rest.

|                       | Rest |    | Exercise Session | Recovery |    |    |
|-----------------------|------|----|------------------|----------|----|----|
|                       | 15   | 20 | 45               | 10       | 20 | 30 |
| Advanced Hemodynamics |      |    |                  |          |    |    |
| Arterial Stiffness    |      |    |                  |          |    |    |

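### The before-and-after averaging rule fills a missing 10-min value from pre-exercise Rest and the 20-min value, interpolating across the class, and cannot be applied at Rest or 30 min

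*Protocol*

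**What the plan says.** The Statistical Analysis and Data Monitorization section of the protocol expects that, for technical reasons, "missing data (~4–5%) may be evident during the study", and that these data "subsequently should be replaced by averaging values before and after the missing value for the relevant variable prior to analysis". It makes no exception for any time point and gives no separate rule for the first or last reading.

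The schedule is in the Design section. "Participants will attend 4, separate, intervention sessions", three of them exercise classes and one a seated control. Each session starts with supine rest. Of the middle part the text says: "Exercise sessions will consist of either a 45-minute class of Bike, Pump Power, and Global Training"; Control sits for the same time. Afterwards "hemodynamic and stiffness indices are reevaluated at 10, 20- and 30-min following recovery and compared to those at rest".

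The main analysis is a two-way repeated-measures ANOVA (intervention × time), adjusted for sex and activity energy expenditure. It compares interventions "over time (Rest vs. post-intervention time points) for indices of autonomic and vascular function", with Bonferroni post-hoc tests. The stated purpose is to "compare the time-course of post-exercise parasympathetic reactivation of the heart" and changes in arterial stiffness between classes.

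**The concern.** Averaging the two neighbours of a gap is reasonable when the series is smooth through the gap. Here the experimental intervention lies between the first reading and the second. Within a session, the value before the 10-min reading is the pre-exercise Rest value, so the fill treats the change produced by the class as if it had built up steadily from Rest to 20 min of recovery. The 10-min reading is the earliest post-exercise time point and matters most to a study of the recovery time-course.

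The error has a predictable direction. In the three exercise sessions it pulls the 10-min change toward zero; in Control there is little change to lose. The intervention × time comparison is therefore weakened at that point.

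At the two ends the rule gives no answer. Rest, the reference for every contrast, has no earlier value in its session, and 30 min has no later one. Someone would have to decide after seeing the data, or borrow a value from another session, which would mix different randomised conditions.

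**Working it through.** The protocol gives no figure to reproduce beyond the 4–5%, so the check is algebra on its schedule.

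**Inputs from the protocol:** four sessions; four time points (Rest, 10, 20, 30 min); 4–5% missing; 12 participants (Participants section: "Twelve apparently healthy adults aged between 21 to 34 years will be included in this study"). The power calculation gives 22 instead. That conflict is a separate matter, so counts are shown for both.

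**Assumptions:** r = D20/D10, where D10 and D20 are the true changes from Rest at 10 and 20 min. The protocol gives neither, so r is varied. Missingness is taken as unrelated to the response and, unless stated, equal at all time points.

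**Step 1: one filled 10-min value.** Fill = (Rest + value at 20 min)/2. Its change from Rest is D20/2 = (r/2) × D10. Share of the response lost = 1 − r/2.

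**Step 2: the condition mean at 10 min.** If a share p of the cell is filled, dilution of the mean response = p × (1 − r/2).

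| r | Lost per filled value | Dilution, p = 4% | Dilution, p = 5% | One gap in 12 (p = 1/12) |
|---|---|---|---|---|
| 1.25 (still growing) | 37.5% | 1.5% | 1.9% | 3.1% |
| 1 (plateau) | 50% | 2.0% | 2.5% | 4.2% |
| 0.75 | 62.5% | 2.5% | 3.1% | 5.2% |
| 0.5 | 75% | 3.0% | 3.8% | 6.3% |
| 0.25 | 87.5% | 3.5% | 4.4% | 7.3% |
| 0 (back to rest by 20 min) | 100% | 4.0% | 5.0% | 8.3% |

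**Step 3: how many gaps have no rule.** Readings per variable = n × 4 × 4.
- n = 12: 192 readings, 7.7–9.6 missing. Of these, 1.9–2.4 fall at 10 min and 3.8–4.8 at Rest or 30 min.
- n = 22: 352 readings, 14.1–17.6 missing. Of these, 3.5–4.4 fall at 10 min and 7.0–8.8 at Rest or 30 min.

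Half of the expected gaps therefore fall where the rule lacks a neighbour.

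**Step 4: the 20-min value.** Fill = (value at 10 min + value at 30 min)/2. This is ordinary linear interpolation within recovery and does not cross the class. The filled value is still analysed as if it had been observed.

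**Step 5: would dropping incomplete participants do instead?** With independent gaps over 4 × 4 = 16 cells, the chance of at least one gap is 1 − 0.96^16 = 48% to 1 − 0.95^16 = 56%. Of 12 participants, about 6 to 7 would be lost for a given variable.

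**The case against.** The strongest counter-argument concerns size. The loss applies only to a value that is filled, and at the stated missingness the mean 10-min response moves by a few per cent. That would not overturn a comparison between classes. This stands, and it limits the point's weight.

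Four stronger readings are tempting, and the protocol does not support them.

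- A reader might infer that 10-min readings in general are averaged with Rest. They are not: an observed 10-min reading is left alone.
- A reader might infer that most of the exercise response is erased. Even for a filled value, more than half is lost only if the response fades between 10 and 20 min. The purpose makes fading plausible for autonomic indices, but the background section reports variable results across exercise modes, and no response shape is given for stiffness.
- A reader might put every gap in the three post-exercise 10-min cells: 4.5% × 16/3 = 24% of those cells, hence a dilution of 12% at r = 1 or 18% at r = 0.5. That is a worst case. The protocol attributes gaps to technical issues and does not say that they cluster.
- A reader might infer that the residual error is always understated. An average of two readings is less variable than one, but a filled 10-min value is also displaced from its cell mean by (1 − r/2) × D10, which adds variance. The net effect at 10 min can go either way.

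The rule can also be read differently for densely sampled signals: continuous heart rate and pressure, beat-to-beat intervals and 1-min gas averages. There, the values before and after may mean adjacent samples, and the filling is harmless. The protocol does not say which reading applies. This does not help PWV or the ultrasound indices.

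Figure 2 shows two rest columns, at 15 and 20. If a variable had both, a missing later rest value would have two neighbours, but one would be the post-exercise 10-min reading, so the baseline would be contaminated instead.

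**Conclusion.** The defect is real for indices measured only at the four time points. The protocol fixes a rule that interpolates across the intervention at 10 min and has no value to offer at Rest or 30 min. Each filled 10-min value loses 1 − r/2 of its response. On the mean 10-min response the effect is about 2–4% for r from 1 down to 0.25 with evenly spread 4–5% missingness, and about 4–7% in a 12-person cell with one gap. It is larger if gaps cluster at 10 min after exercise and smaller if the response is still growing. These sizes rest on assumed values of r and on gaps unrelated to the response.

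This should be fixed before analysis. The bias is modest, but it runs toward no difference, and about half of the expected gaps would be left to decisions made after the data are seen.

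**What to change.** Delete the averaging rule for time-point data. At the least, state that no value is interpolated across the class or between sessions, and say what is done when Rest or 30 min is missing. If adjacent-sample interpolation within a continuous recording is intended, say so separately and name the signals.

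Analyse all observed values with a linear mixed model: fixed effects for intervention, time and their interaction, the planned covariates, random effects for participant and for session within participant, and Bonferroni post-hoc comparisons as planned. This needs no imputation and is valid if data are missing at random. Report the number of missing values by condition and time point, so that any clustering can be seen.

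The cost is a change of wording and respecification of the ANOVA, covariate adjustment and post-hoc tests in a mixed-model procedure. No extra data or visits are needed. A repeated-measures ANOVA restricted to complete participants is not a substitute, given the share of participants that it would be expected to lose.
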